## Abstract

**Background:**

Childhood asthma is a prevalent chronic disease that affects millions of children worldwide. Managing this disease demands not only medical treatment but also the long-term self-management efforts of both children and their parents. Conventional self-management education typically depends on face-to-face approaches, often failing to take into account the personalized requirements and ongoing support needed. Nevertheless, with the evolution of artificial intelligence (AI) technology, fresh prospects have emerged to boost the effectiveness of self-management for childhood asthma. Based on it, we have designed an AI Health Education Accurately Linkage System (AI-HEALS) to explore whether AI-driven interventions can improve self-management capabilities of families with asthmatic children, thereby helping them control the disease and reduce medical costs.

**Methods:**

This research is a pilot single-blind randomized controlled trial (RCT) intended to gauge the efficacy of the AI-HEALS intervention delivered via the WeChat platform in enhancing the self-management abilities of families with asthmatic children. Participants will be recruited from eligible families whose children have been diagnosed with asthma and randomly allocated to either the intervention group or the control group. The control group will receive standard treatment, whereas the intervention group will receive both standard treatment and the AI-HEALS intervention. The intervention includes an AI-enabled, voice-activated interactive question-and-answer system, as well as monitoring and recording of physiological indicators, regular reminders, and customized educational articles. All components of the intervention will mainly be provided through a WeChat official account named “Children’s Asthma Health Management Expert.” AI-HEALS will construct its knowledge base according to pediatric asthma treatment guidelines to enhance the accuracy and reliability of the information it offers. The primary outcome measure is the alteration in asthma symptom control levels, while secondary outcomes comprise a variety of other physiological indicators related to asthma, parents’ self-management behaviors, and mental health conditions.

**Discussion:**

This study combines AI and mobile health technology to develop the AI-HEALS system, with the aim of assisting families of children with asthma in controlling the disease symptoms. The primary objective is to evaluate whether the intervention can improve asthma symptom control.

**Clinical trial registration:**

The study is scheduled to begin in April 2025 and is expected to conclude in December 2026. This research protocol is the first version and was registered with the China Clinical Trial Registration Center on February 14, 2025 (Registration Number: ChiCTR2500097233).

## Introduction

1

Childhood asthma ranks among the most prevalent chronic diseases in children globally. A report from the World Health Organization indicates that around 260 million people worldwide are affected by asthma, with roughly 10% of these cases occurring in children (1, 2). The prevalence of asthma varies significantly across countries, exhibiting distinct trends and characteristics (2, 3). In the African region, current and lifetime asthma prevalence rates are the highest, at 13.2% and 11.3% respectively (2, 3). By contrast, the Americas have the lowest current asthma prevalence, which is 10.0%, while Southeast Asia reports the lowest lifetime asthma prevalence, at 8.8% (2, 3). Moreover, environmental factors associated with urbanization, lifestyle changes, as well as genetic factors, are all regarded as crucial factors contributing to childhood asthma development (4, 5).

Childhood asthma does not merely lead to recurrent wheezing, coughing, and breathing difficulties (6, 7). It can also trigger severe acute episodes that pose direct threats to the child’s life (6, 7). Additionally, asthma can have long-term implications for both the physical growth and mental health of children (8, 9). For example, school-aged children might have to miss school, leading to declining academic performance, and experience challenges with self-esteem and social skills due to their condition (8, 9). From a family perspective, the long-term management of asthma imposes a significant burden on daily life (10, 11). Families must continuously adapt their daily routines to meet the child’s medical requirements, like making frequent trips to the hospital and consistent medication administration (10, 11). Moreover, parents often endure heightened psychological stress and financial strain, especially in areas with scarce healthcare resources, where this burden is particularly pronounced (10, 11). Beyond the impact on individuals and families, childhood asthma also imposes substantial economic burdens on public health systems (12). One study estimates that over the next 20 years, asthma will incur approximately $300 billion in direct healthcare costs in the United States alone (13).

At present, the interventions for childhood asthma primarily comprise two major categories: pharmacological and non-pharmacological treatments. Pharmacological treatment relies on short-acting and long-acting bronchodilators, along with corticosteroids. These medications are critical for managing symptoms and preventing exacerbations (14, 15). In terms of non-pharmacological treatments, they include educational interventions, environmental control, and lifestyle adjustments. For instance, children are advised to avoid tobacco smoke and household allergens while increasing physical activity (14, 16). Although the existing intervention strategies demonstrate effectiveness, they face notable limitations and challenges. Firstly, pharmacological treatments may lead to dependency issues (17). Prolonged use may cause adverse effects, and their efficacy may vary among children (17). Secondly, non-pharmacological treatments require significant resources from both the family and the larger social environment. As a consequence, their implementation is not only difficult but also costly (6, 16). Additionally, current interventions are often not personalized, failing to fully account for individual circumstances and needs while inadequately integrating patient education and behavioral support (6). Given these limitations, the development of novel therapeutic strategies is urgent, particularly those leveraging digital health technologies and mobile health platforms.

Nowadays, more than 75% of the global population has access to the internet via mobile devices, and over 57% of households are connected to the internet. This clearly shows the wide-spread presence and importance of mobile internet in modern life, notably in health management and lifestyle adjustments. Research on the effectiveness of mobile health interventions and digital health interventions for patients has been conducted (18, 19). Mobile health applications have developed from simple voice and text message services to complex smart applications that incorporate various health behavior change programs (18–20). These interventions now address a broad range of conditions, including pain management, chronic disease management, weight control, and smoking cessation (18, 19). In recent years, mobile health interventions in asthma management have emerged as promising tools. For example, a randomized trial of the AIM2ACT program conducted by Fedele et al. demonstrated clinically significant improvements in asthma control among adolescent patients, accompanied by high participant satisfaction and engagement rates (21). Similarly, an evaluation of the “Breath Kit” mobile application led by Smith et al. reported significant improvements in inhaler technique adherence, with high user satisfaction and preference for digital delivery over traditional methods (22). Furthermore, a longitudinal study of the MASK-air^®^ application conducted by Kvedarienė et al. indicated high satisfaction levels and symptom improvements, with many patients recommending the app to others (23).

The Artificial Intelligence Health Education Precision Accurately System (AI-HEALS) is implemented via WeChat, China’s largest social platform with over 1.2 billion monthly active users. This platform can leverages WeChat’s ecosystem integration (Mini Programs, official accounts, payment systems) to embed health services into daily user behavior, overcoming retention challenges of standalone apps. Its demographic reach across urban/rural areas and older adults ensures equitable access, while closed-group chat and privacy features address health data sensitivity. Compared to platforms like Weibo (public content focus), WeChat’s social communication capabilities foster sustained peer support critical for behavior change. Based on it, this system utilizes low-cost, widely accessible mobile communication technology to deliver convenient and continuous disease management support directly to patients’ homes. AI-HEALS is grounded in a comprehensive theoretical framework that integrates the Multi-Theory Model (MTM) of health behavior change with the Health Action Process Approach (HAPA), forming the HAPA-MTM model (24, 25). This model is composed of three key phases: the pre-intentional phase, providing a comprehensive and continuous framework for health promotion. Interventions based on this model feature core components including: an intelligent question-and-answer system with voice interaction capabilities built on a proprietary knowledge base, monitoring of physiological parameters and behavioral patterns, customizable reminder systems, and personalized health content delivery. This innovative intervention framework is expected to better meet modern health management demands while providing evidence-based solutions for childhood asthma patients and their families.

In summary, this study aims to assess the effectiveness of the AI-HEALS intervention program for childhood asthma management through a pilot randomized controlled trial (RCT) across the following dimensions: asthma control, quality of life, medication adherence, and mental health outcomes.

Assess the extent to which a three-month intervention program grounded in the AI-HEALS improves clinical outcomes in childhood asthma patients’ physiological indicators.Evaluate how effectively the three-month comprehensive intervention program can improve the psychological indicators of the parents of children with asthma.Ascertain the effectiveness of the three-month comprehensive intervention program in promoting self-management behaviors among the parents of children with asthma.

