Children’s Asthma Knowledge-Based Intelligent Question-Answering System (KBQA): This program aims to help parents of asthmatic children better understand asthma. It plays a role through the FAQ robot (FAQrobot), so that families can efficiently and accurately obtain the knowledge related to childhood asthma. In order to achieve this goal, we will develop a thorough and accurate knowledge base around childhood asthma. The knowledge base will cover a wide range of aspects, including the basic concepts of disease, etiology, symptoms, treatment methods, drug use, daily management, appropriate diet and appropriate sports activities. We will integrate this knowledge base into the large language model of Doubao (developed by ByteDance). In this way, the model can learn from the database and provide professional answers to patients’ questions directly on the WeChat platform. In addition, in order to enhance the interaction and user participation, the system will ask three related questions each time the user queries. This encourages users to explore further and interact more deeply with the system. In order to continuously optimize the knowledge base and better meet the needs of users, we will record the query and usage behavior of participants at the back end of the system, such as the time and frequency of accessing the system. By analyzing this data, we can identify the patterns of participants’ behavior. Based on these insights, we will be able to adjust and improve the knowledge base and question-and-answer system to ensure that the information is up-to-date and accurate. In the whole question-and-answer interaction process, the system supports text and voice input. This greatly reduces the threshold for users operating the system, so that more people can access the system.Recording and Monitoring of Physiological Indicators and Lifestyle Changes: In this study, the AI-HEALS will be used to encourage childhood asthma families to regularly record lifestyle factors, including weekly medication adherence, dietary habits, and physical exercise. Participants can directly input data into the system, allowing researchers to review recorded content in real-time through a backend interface, enabling long-term tracking and monitoring of self-management behaviors. To ensure data relevance and accuracy, the research team will jointly develop SMART (Specific, Measurable, Achievable, Relevant, Time-bound) plans with families during the initial phase of engagement. Data collection processes will be structured around these plans, with system-generated reminders sent every Saturday prompting detailed information uploads. This approach allows comprehensive assessment of intervention impacts on patients’ daily lives while ensuring data alignment with family-specific goals.Customized Reminder Services: In order to improve treatment compliance, the AI-HEALS system will provide a personalized reminder service. Participants can flexibly set reminders for various important tasks, such as medication and exercise. Once these reminders are set, the system will automatically send notifications at the specified time. This reminder service is designed to help patients strictly abide by medical advice, promote the long-term sustainability of healthy behaviors, and ultimately help to better control asthma.Automated and Personalized Asthma Science Articles for Family: The system will also run a mechanism to automatically distribute educational articles. Every week, families of children with asthma will automatically receive one to three articles on asthma management. These articles will cover a variety of topics. It includes dietary recommendations, such as which foods are good for asthmatic children and which foods should be avoided. Sports suggestions will also be provided to guide children to carry out sports activities of the appropriate type and intensity. It will also provide information on the correct medication, such as the correct method of medication and potential side effects that should be paid attention to. According to the interactions between the family and the system, such as the types of questions they raised, the frequency of visits, and the topics they are more interested in, targeted educational articles will be pushed accurately to meet the unique needs of each family. In order to maximize the effectiveness of information dissemination, the research team will regularly review the background data. This includes analyzing the number of articles that the participants visited, the different types of articles they liked, and the length of time they spent reading each article. According to this data, the article content and dissemination frequency will be adjusted.

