#### Secondary outcomes

2.9.2

Physiological Control of Children: The assessment indicators cover multiple aspects. In terms of pulmonary function, key parameters such as pulmonary ventilation function and expiratory flow rate will be detected by professional equipment; the average number of days with asthma symptoms, record the number of days when children experience asthma-related symptoms within a certain period; the number of nights awakened due to asthma symptoms; the number of days with activity limitations due to asthma; the number of days per week requiring inhaled bronchodilators for symptom relief; height, weight, waist circumference, body mass index (BMI); the 30 - day readmission rate; the length of hospital stay.Parental Behavior Changes: Parental behavioral changes will be measured using specific instruments, including a self-developed questionnaire to assess frequency and exposure to smoking and alcohol consumption; the Pittsburgh Sleep Quality Index Short Form (PSQI-SF) to evaluate sleep patterns; and the EQ-5D-5L (EuroQol-5 Dimensions 5 Levels) scale for measuring overall quality of life.Parental Social Cognition and Psychology: Self-efficacy; depression, anxiety, stress levels; social support.

In addition, the recruitment rate, dropout rate, and reasons for withdrawal will be collected. During the data analysis phase, in order to assess the homogeneity of the data, the demographic characteristics and study outcomes of those who dropped out will be compared to determine whether the dropout situation has an impact on the overall effectiveness of the study.

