Based on this, the study will conduct a pilot randomized controlled trial to assess the effectiveness and acceptability of the AI-HEALS system in controlling asthma in children. The main purpose was to evaluate whether the intervention of C-ACT measurement after the intervention improved the control of asthma symptoms. Secondary outcomes include physical health indicators such as lung function, BMI, and hospitalization rates, as well as behavioral and psychological outcomes related to parental involvement, self-management strategies, and overall child quality of life. These outcomes will be measured using quantitative methods (e.g., standardized questionnaires and physiological assessments) and qualitative interviews. Given the medical and behavioral factors involved in childhood asthma, AI-HEALS has great potential to increase patient engagement and improve adherence to treatment regimens.

Although the interventions proposed in this study show considerable potential, some limitations must be recognized. First, the generalizability of the findings may be limited by inclusion criteria that focus on specific populations and clinical characteristics. For example, this study focused on children with asthma who were willing to use digital health interventions and may not have included those with lower health literacy or those less comfortable using technology. Second, while this study will provide valuable insights into the efficacy of the AI-HEALS system, there may be challenges in interpreting the numerous external factors that influence asthma control. Environmental triggers, socioeconomic status, and access to healthcare are all important variables that may influence outcomes, but it may be difficult to fully control for them in the real world. This study will include demographic and clinical covariates in its analysis in an attempt to account for some of these factors, although residual confounders may still affect outcomes. Finally, although the study aims to ensure data accuracy through rigorous monitoring procedures, issues such as participant dropout or missing data may still affect the validity of the findings. The research team plans to use multiple interpolation techniques to address these challenges, but the potential bias of missing data must still be considered.

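### Medication adherence and parental self-management are stated aims, but no listed outcome measures adherence, and self-management is covered only by generic measures

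*Protocol article*

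**What the plan says.** Four places set the aims:

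- The closing summary of the Introduction commits the trial to assessing effectiveness "across the following dimensions: asthma control, quality of life, medication adherence, and mental health outcomes".
- The third objective is to "Ascertain the effectiveness of the three-month comprehensive intervention program in promoting self-management behaviors among the parents of children with asthma".
- The Abstract (Methods) says the trial gauges the efficacy of AI-HEALS "in enhancing the self-management abilities of families with asthmatic children", and its list of secondary outcomes includes "parents’ self-management behaviors, and mental health conditions".
- The Discussion again counts "self-management strategies, and overall child quality of life" among the secondary outcomes.

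The measures are set in 2.9, 2.10 (Table 1) and 2.11. Section 2.9.2 gives parental behaviour change as "a self-developed questionnaire to assess frequency and exposure to smoking and alcohol consumption", a short sleep index and the EQ-5D-5L. Self-efficacy is listed separately, under social cognition and psychology.

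Adherence recording appears in 2.7.2, as one of the four AI-HEALS components. The system will "encourage childhood asthma families to regularly record lifestyle factors, including weekly medication adherence, dietary habits, and physical exercise", with a prompt every Saturday and a backend view for the researchers. The same section says AI-HEALS is delivered to the intervention group. Control care (2.7.1) includes education on adherence but describes no measurement of it.

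**The concern.** An effect on adherence can be estimated only if adherence is measured in the same way in both arms. Here it is named as an effectiveness dimension, but no outcome is attached to it. The one place where it is recorded is a component of the treatment under test. A log that prompts families weekly and feeds reminders and tailored content cannot supply a between-arm contrast, because the recording is itself part of what differs between the arms.

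Two things are at stake. The report could not answer a question the trial says it asks, or the intervention-arm logs might be presented as if they answered it. In addition, 2.4 justifies the sample partly by the wish to learn how variable the outcomes are. A later trial would get no such estimate for adherence under usual care.

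**Working it through.** No figure of the plan is in dispute, so the check maps each stated aim to the outcome list, Table 1 and the instrument descriptions.

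| Stated aim | Measure in the plan | Scheduled times | Comparable between arms? |
|---|---|---|---|
| Asthma control | C-ACT (primary) | Baseline, discharge, 3 months | Yes |
| Quality of life | EQ-5D-5L (listed as a parental measure) | Baseline, 3 months | Yes |
| Mental health | PHQ-4 | Baseline, discharge, 3 months | Yes |
| Medication adherence | None; AI-HEALS weekly log only | Not in Table 1 | No |
| Parental self-management (third objective) | Smoking, alcohol, sleep | Baseline, 3 months | Yes, but generic |
| | NGSES-SF (general self-efficacy) | Baseline, discharge, 3 months | Yes, but generic |

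**Step 1: Table 1.** Apart from eligibility, consent, allocation and sociodemographic variables, it has 12 rows: C-ACT, lung function, s-EMBU-C, PHQ-4, PSSS-SF, NGSES-SF, EQ-5D-5L, smoking, alcohol, B-PSQI, FCS-SF and eHEALS. None records adherence or asthma self-management. FCS-SF and eHEALS are baseline only.

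**Step 2: instruments.** Section 2.11 describes 11 questionnaires. None concerns taking prescribed treatment, inhaler technique or asthma management at home.

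**Step 3: nearest substitutes.** Section 2.9.2 lists weekly days of reliever use. That reflects symptom need, not adherence to prescribed treatment. The NGSES-SF has three items on general confidence and none on asthma.

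**Step 4: where adherence is recorded.** Section 2.7.2 is the only place that describes a recording route, and that route is the AI-HEALS system.

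**Step 5: the inclusion criteria.** Section 2.3.1 asks every caregiver to be willing and able to upload daily records and gives adherence logs as an example. It names this alongside AI-HEALS consultations and system-delivered articles. It gives no upload route for control families, no schedule and no use of the logs as an outcome.

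**Result.** Of the four dimensions in the Introduction, 3 have a scheduled both-arm measure and 1 (adherence) has none. The third objective has both-arm measures, but none specific to asthma.

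**The case against.** **Third objective.** The three objectives (physiological, psychological, behavioural) broadly match the three outcome groups in 2.9.2, so the parental behaviour group can be read as the plan's own definition of the third objective. Its components are scheduled for all participants, and the Introduction itself links tobacco smoke to asthma management. This stands. The complaint there is that the measures are generic, not that data are absent.

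**Inclusion criterion.** Because 2.3.1 mentions adherence logs for every caregiver, a reader who infers that none of the 30 control families will have adherence data goes beyond the text. The documents leave it unclear. What they do not provide is a declared both-arm adherence outcome.

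**Article format.** A journal article condenses a fuller protocol. That carries little weight here, since this article itemises its outcomes, tabulates the schedule and gives scoring detail, even for scales used only at baseline. Naming adherence as a dimension and then omitting it from all three places is a mismatch within the text.

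**Pilot status.** Section 2.4 disclaims hypothesis testing. The gap remains, because estimating outcome variability also needs control-arm data.

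**Wider readings that the text does not support:**

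- *The symptom-day, night-waking, activity-limitation and reliever counts have no scheduled visit.* They have no row in Table 1, but neither do height, weight and waist circumference, which 2.10 expressly measures. Absence from the table is weak evidence.
- *Those counts come from platform records and are therefore measured differently by arm.* Nothing says so. The log in 2.7.2 is described for adherence, diet and exercise, and section 3 promises the same survey times and questionnaires in both groups.
- *Child quality of life is an unmeasured aim.* This rests on one sentence in the Discussion. The Introduction says only quality of life, so it is a wording correction.

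**Conclusion.** The point holds in limited form. Medication adherence is a stated effectiveness dimension with no declared measure in both arms, and the self-management objective is covered only by generic behaviours and general self-efficacy. Following the plan as written gives no between-arm conclusion on adherence or asthma-specific self-management.

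A reader might infer that the trial cannot compare the arms on its main question. It can: the main question is asthma symptom control, measured by C-ACT at three time points in both arms, and quality of life and mental health are also comparable.

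The conclusion assumes that the outcome list and Table 1 are the intended set of questionnaire outcomes, and that the adherence logs in the inclusion criteria refer to the AI-HEALS recording component. If a both-arm adherence log was intended, the defect is that it is not declared as an outcome and no control-arm route is given. The remedy is then to state both.

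This should be corrected, but it does not threaten the primary outcome.

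**What to change.** Preferred: add to 2.9.2 and Table 1 one short caregiver-reported questionnaire on medication adherence and asthma self-management, with identical items and administration in both arms at baseline and 3 months. State in 2.7.2 or 2.12 that AI-HEALS logs are process data describing engagement and will not be used for between-arm comparison. Clarify in 2.3.1 whether the adherence logs apply to control families.

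Alternative: remove medication adherence from the aims in the Introduction, restate the third objective as the parental behaviours actually measured, and align the Abstract and Discussion.

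Cost: a few extra minutes per family at two visits already planned, or wording only for the alternative. Section 2.3 puts the start of enrolment at April 2025, so some families may already be past baseline. They can still contribute to a 3-month comparison, which randomisation supports without a baseline value, though with less precision.
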